#### Follow-up

Following the initial presentation to the ED, patients will be followed up to the time of hospital discharge. Data will be collected from the clinical records of the patient, including, but not limited to:

GCS on arrival in hospital.Details of the clinician’s assessment of the CCHR.Outcome of any brain imaging (ie, CT and/or MR scans, recorded as part of routine practice).AIS in relation to head injury.Injury Severity Score.Mortality status.Neurosurgical procedures and/or surgery.

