### Measuring and defining outcomes

Feasibility outcomes will be assessed using screening logs and case report forms (CRFs) completed by attending paramedics during the course of the study. At the end of the study period, a minimum of two clinicians (affiliated with the relevant NHS trusts) will review in-hospital patient records to diagnose the secondary outcomes of this feasibility study (neurosurgically significant TBI, abnormal CT findings and death within 7 days). A third independent investigator will be invited to adjudicate any discrepancies. Diagnostic adjudication will be blinded to the final interpretation of the CCHR. Additionally, a neuroradiology consultant/expert will be consulted in case of the CT scan diagnosis is inconclusive.

Neurosurgical interventions are defined as any neurosurgical intervention including intracranial pressure monitoring or an Abbreviated Injury Scale (AIS) with the severity ≥3 in the head region. Abnormal head CT findings will be classified as normal or abnormal and are defined as at least one of the following: skull fractures, intracranial lesions, such as cerebral contusion and traumatic intracranial haemorrhages, or other clinically significant findings requiring hospital admission, neurosurgical interventions and routine follow-up.

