#### In-hospital environment

REDCap will be used to collect hospital data, and a paper CRF will also be available as an alternative. Emergency physicians at the receiving hospital will assess the patients to determine whether a CT scan is necessary in accordance with local and national guidelines. Relevant data about imaging studies undertaken and their findings will be extracted from hospital records. The routine radiology reports will be used to extract the follow-up data required for this study. Where there is uncertainty about the interpretation of the radiology report, a second radiologist will be asked to interpret the images.

Further, emergency physicians at the receiving hospitals will be asked to assess the patients using the CCHR and record their findings, blinded to the assessments made by participating paramedics. These data will be used to determine the interobserver reliability of the CCHR between paramedics in the prehospital environment and clinicians in the ED. Additionally, in-hospital medical records will be reviewed to obtain information regarding neurosurgical interventions undertaken during the patient’s hospital admission.

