### Data analysis

#### Quantitative data

A descriptive analysis will be conducted based on the baseline data for patients enrolled in the study to characterise the demographic and clinical profile. This will include the number of eligible participants who were approached, the proportion who consented to participate, data completeness (expressed as number and percentage) for each variable collected and number and percentage of participants completing follow-up. We will also report recruitment data as rates (number of participants enrolled per week across the study period).

The interobserver reliability between paramedics and emergency physicians’ use of the CCHR will be calculated using Cohen’s kappa, a statistical method for measuring agreement between two observers, together with 95% CIs. Additionally, we will report upon the CCHR’s diagnostic performance for ruling out clinically significant TBI. This will be achieved by calculating the sensitivity, specificity, positive and negative likelihood ratios with 95% CIs against a reference standard of traumatic intracranial lesion, which will be identified from in-hospital records. Given the nature of this feasibility study, the analyses will be viewed as exploratory, preliminary and will be descriptive in nature. Furthermore, to determine the acceptability of the CCHR, the OADRI average item scores will be calculated, with higher scores indicating greater acceptability.

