#### Progression criteria

This feasibility study will be overseen and governed by the Trial Steering Committee (TSC), which will include the chief investigator, principal investigator, two lay members, topic experts in TBI and one paramedic. The role of the TSC is to provide external oversight and to ensure that the study is conducted in compliance with Good Clinical Practice guidelines.^31 32^

The traffic light approach (green/amber/red), also known as a (stop–amend–go) rule, will be used to determine whether or not to proceed with a full definitive trial.^33^ Green (go) indicates that the study meets the preset criteria, and that it would be feasible for a full-powered definitive trial to be conducted without any modifications to the study protocol. Amber (amend) indicates that further feasibility work or modifications to the protocol are required before proceeding with the full trial. Red (stop) indicates that proceeding to a definitive study is not recommended. Taking into account the feasibility outcomes, as well as qualitative interviews with patients and paramedics, a decision will be made regarding whether or not to proceed with the trial or whether to make any amendments to the study design. The progression criteria are shown in table 2.

**Table 2 T2:** Progression criteria to proceed with a definitive trial

	Contributing data	Green (proceed to a definitive trial)	Amber (proceed to a definitive trial following some changes to the protocol)	Do not proceed to a definitive trial
Screening	Training and delegation logs	At least 20 paramedics at participating ambulance hubs trained and on delegation logs	At least 10 paramedics at participating ambulance hubs trained and on delegation logs	Less than 10 paramedics at participating ambulance hubs trained and on delegation logs
Recruitment acceptability	Screening & recruitment log	≥80% of eligible screened patients are consented to take part	≥60% of eligible screened patients are consented to take part	<60% of eligible screened patients are consented to take part
Retention	Screening & recruitment log	Retention of ≥90% of study participants until study completion	Retention of ≥80% of study participants until study completion	Retention of <80% of study participants until study completion

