### Safety considerations, adverse events and serious adverse events

Given the nature of this study, any risk to participants is very low. It is important to note that this study is observational in nature: a patient’s participation in this study will have no effect on the quality of medical care they usually receive in both prehospital and hospital settings. Our study will have no impact on the decision to undergo a CT scan as this will be undertaken at the discretion of the treating clinician, as part of routine clinical care, in accordance with current national guidance. The study will also have no effect on the decision to transport patients to the hospital. There are also small risks associated with data management, but we have carefully considered how data will be handled during the study and we will operate in accordance with current legislation and the standard operating procedures of the sponsor organisation to mitigate that risk. We are not aware of any potential risks this study would pose to the researchers.

Because of the low-risk nature of the study, we do not anticipate any adverse events (including serious adverse events) as a result of participating in this research. However, given the patient group (patients with suspected TBI), we anticipate that many patients will experience expected adverse events, which are related to their initial injury. We will not ask sites to report expected adverse events. Expected serious adverse events include, for example, death due to head injury, neurosurgical procedures for TBI, admission to hospital for traumatic brain injury and loss of function due to TBI. Unexpected adverse events and serious adverse events should be reported. Adverse events will be defined in accordance with ICH (International Council for Harmonisation)Good Clinical Practice as any untoward medical occurrence in a participant, but will only be reported if this was not expected as a result of the patient’s condition, up to the point of handover in hospital.

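### Death within 7 days is an adjudicated outcome, but follow-up ends at hospital discharge, so day-7 status is not ascertained by design for anyone discharged earlier

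*Protocol article*

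**What the plan says.** All references are to the protocol article.

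- **Outcome.** Measuring and defining outcomes lists the secondary outcomes as "neurosurgically significant TBI, abnormal CT findings and death within 7 days". At least two clinicians "will review in-hospital patient records to diagnose the secondary outcomes of this feasibility study", at the end of the study period.
- **Follow-up window.** The Follow-up section says that "patients will be followed up to the time of hospital discharge". Mortality status is among the items taken from the clinical records.
- **Neurosurgery.** Under In-hospital environment, "in-hospital medical records will be reviewed to obtain information regarding neurosurgical interventions undertaken during the patient’s hospital admission".
- **CT.** The safety section says of the CT decision that "this will be undertaken at the discretion of the treating clinician, as part of routine clinical care".
- **Accuracy analysis.** Quantitative data computes sensitivity and specificity "against a reference standard of traumatic intracranial lesion, which will be identified from in-hospital records".
- **Progression.** Completeness of follow-up is a listed feasibility outcome, and the green level for retention in Table 2 is "Retention of ≥90% of study participants until study completion".

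**The concern.** A fixed 7-day outcome needs information up to day 7 on every participant. The stated follow-up stops at an event, discharge, that may come much sooner in patients with GCS 13–15 and no other injury needing treatment. The article describes no day-7 contact, search for re-attendance or check on deaths.

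Three things are at stake. First, the 7-day death count would be read as complete when absence of a record may only mean that nobody looked. Second, a lesion that comes to light after discharge would not reach the reference standard, and this error favours the rule if the patient was rule-negative and unscanned. Third, the study exists to test the processes of a definitive accuracy study, and its retention criterion can be met without showing that outcomes after discharge can be obtained.

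**Working it through.** **1. The plan's own figure.** The only recruitment figure that can be rebuilt is the 1100 eligible patients: 5332 / 57 months × 6 months × 2 centres = 1122.5, within about 2% of 1100. The further reduction to about 100 recruits has no stated formula. The point does not depend on either number; 100 is used below as a convenient denominator.

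**2. The windows side by side.**

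| Item | Window or source stated |
|---|---|
| Death | within 7 days |
| Follow-up data, including mortality status | to hospital discharge |
| Neurosurgical intervention | during the admission |
| Traumatic intracranial lesion | in-hospital records; CT only where the clinician orders it |
| Adjudication | in-hospital records, end of study; no instruction to search beyond the index attendance |

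The first two rows cannot both hold for a participant who goes home before day 7.

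**3. How many participants this touches.** The article gives neither an admission rate nor a length of stay for this cohort. A lower bound follows if every admitted patient is assumed to stay at least 7 days and every other patient goes home earlier:

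discharged before day 7 ≥ 100 × (1 − admission rate)

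| Admission rate | Source | At least this many of 100 |
|---|---|---|
| 4% | Introduction, background figure | 96 |
| 9% | Introduction, background figure | 91 |
| 20% | assumption | 80 |
| 30% | assumption | 70 |
| 40% | assumption | 60 |

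The majority of participants would cease to be affected only if half or more were still in hospital at day 7.

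**4. What one late-found lesion would do to sensitivity.** The event counts are assumed. The intervals are exact (Clopper–Pearson) 95% intervals.

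| Lesions observed, all rule-positive | Sensitivity as observed | With one further lesion, found after discharge in a rule-negative patient |
|---|---|---|
| 5 | 5/5 = 100% (48% to 100%) | 5/6 = 83% (36% to 99.6%) |
| 10 | 10/10 = 100% (69% to 100%) | 10/11 = 91% (59% to 99.8%) |

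The error arises if an unscanned patient with no lesion on record is classed as lesion-free. That patient then counts as a true negative instead of a false negative.

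**5. The retention criterion.** If 100 of 100 participants are retained to discharge, retention is 100% and green. At 9% admission, directly observed day-7 status would still be available for at most 100 − 91 = 9 of them. The criterion therefore carries no information on day-7 ascertainment.

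**The case against.** **The end-of-study review may close part of the gap.** For nearly all participants it takes place after day 7, and it is not expressly confined to the index attendance. The list of follow-up items is open-ended and includes mortality status. This stands in part: some re-attendances or deaths at the participating trusts could be seen. But the review is not tasked with finding them, and events at other hospitals or in the community may not appear in those records. It would be too strong to say that every event after discharge is lost; capture is incidental.

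**The accuracy analysis does not use 7-day death.** This stands in full. A reader might infer that missed deaths directly bias sensitivity, but the reference standard is traumatic intracranial lesion. Only a late-found lesion matters there, and that problem owes as much to CT being discretionary as to the length of follow-up.

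**Follow-up can fail in several ways.** A reader might infer that completeness and retention can fail only through withdrawal. The article does not support that. The ED physician's assessment of the rule, the Abbreviated Injury Scale or the Injury Severity Score may be missing. Consent is deferred, and patients entered by proxy must be asked again on regaining capacity. Table 2 also has a separate criterion for outcome data (85% and 60%). What remains is narrower: none of these is stated to require known day-7 status.

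**Early discharges need not be mainly rule-negative.** The Introduction gives a specificity of 36–65% for the original rule. If 95 of 100 patients had no lesion (assumption), that implies 0.36 × 95 = 34 to 0.65 × 95 = 62 rule-negative patients, against 91 to 96 early discharges at the background rates. They could be a minority.

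**The admission figures are weak.** The 9% and 4% are before-and-after background values, not a range for adults brought by ambulance to these centres. Nor does the article support a claim that discharged patients are observed for less than a day.

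**Conclusion.** The point holds and is of moderate weight. As written, death within 7 days is not ascertained by design for participants discharged before day 7. They are probably most of the sample: at least 91 to 96 of 100 at the background admission rates, and at least 60 at an assumed 40%. This is an inference, because the article gives no admission rate or length of stay for the cohort.

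The effect on accuracy is conditional. It needs an unscanned rule-negative patient, a lesion found after discharge, and an analysis that takes that patient as lesion-free. With few events, one such patient moves sensitivity by 9 to 17 percentage points in the illustration above.

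The weight goes no higher because the outcome is secondary, the accuracy analysis is declared exploratory, care is unchanged, and no progression criterion uses 7-day death or accuracy. It is still worth acting on, because the findings are meant to inform the design of the definitive study.

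**What to change.** 1. In Follow-up, extend the window to hospital discharge or day 7 after injury, whichever is later.
2. In the end-of-study record review already planned, search for re-attendance, repeat imaging, neurosurgery and death to day 7 for every participant, and align the neurosurgery sentence under In-hospital environment with this.
3. Report the percentage of participants with known day-7 status as part of completeness of follow-up, so that the retention result in Table 2 can be read beside it.
4. State that events at other hospitals or in the community may remain unknown, and report such participants as unknown, not as event-free.

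If this is not done, rename the outcome as death before hospital discharge. That removes the contradiction but leaves late-found lesions unsought.

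The cost is a short extra look-up per participant, a minor amendment with a check that the information sheet covers the look-up, and a slightly less favourable completeness figure. No patient's care changes.

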### Evaluation of acceptability

We will use a qualitative approach to evaluate the acceptability of trial processes used to study participants. We will purposively sample (a) study participants and (b) paramedics. The intention is to maximise heterogeneity (according to age, sex and ethnic origin, and for paramedics, seniority and base ambulance station). Patients and participating paramedics will be interviewed for the purpose of exploring their experiences of participating in a study of this nature. Previous emergency care research has demonstrated the value of this method in providing information regarding the feasibility and design of a larger study.^21^

To maximise convenience for participants and thereby recruitment, participants will be invited to take part in a semistructured interview either by telephone, face-to-face or video conference. Informed consent will be obtained from all participants. We will explore the factors that facilitate or discourage participation in the research. Paramedics and study participants will be offered a £30 high street voucher to thank them for taking part. Telephone and sign language interpreters will be provided where necessary. The interview topic guides (online supplemental appendix 1) consist of a number of questions and prompts concerning the patients and paramedics’ experiences of participating in this study, as well as the paramedics’ perceptions of the viability of the CCHR. Prior to commencement of the interviews, two pilot interviews will be carried out. To determine the relevance, clarity and duration required to complete each interview, one will be with a paramedic and the other will be with a patient.^22^

10.1136/bmjopen-2023-077191.supp1Supplementary data

The Ottawa Acceptability of Decision Rules Instrument (OADRI) is a 12-item instrument that will be used to measure paramedics’ attitudes toward the CCHR and clinical sensibility.^23^ Paramedics will be asked to provide their level of agreement with 12 statements about the CCHR using a 6-point Likert scale. The first seven statements are worded in such a way that a higher number indicates higher acceptance, while the last five are worded in the opposite manner to minimise the acquiescence bias.^24^

### Consent process

An exception to the normal process of informed consent is established for patients in emergency situations who are unable to provide consent. As stated in the Declaration of Helsinki, ”for a research subject who is legally incompetent, physically or mentally incapable of giving consent or is a legally incompetent minor, the investigator must obtain informed consent from the legally authorised representative in accordance with applicable law. These groups should not be included in research unless the research is necessary to promote the health of the population represented and this research cannot instead be performed on legally competent persons.”^25^

In this study, we will include patients in the prehospital environment who are receiving an emergency ambulance response having sustained a head injury. The nature of this presentation means that the mental capacity to provide informed consent for participation in research will be compromised, especially given the time-critical nature of the emergency medical response. Therefore, we will adopt a deferred consent model, which is widely used in research of this nature.^26^ Deferred consent in the emergency setting is a practice where medical treatment or research participation is initiated without prior consent from patients due to urgent circumstances and their compromised mental capacity, with the intention to obtain consent retrospectively once the patient’s mental capacity has improved.^27^

Paramedics will enrol eligible participants, enabling them to collect the required data. Patient care will be unchanged. We will then seek deferred written informed consent after the patients have received their initial treatment in hospital, and once they have regained their mental capacity.

When seeking written informed consent, a participant information sheet will be provided. Deferred consent may be obtained by either of the following means: (a) a member of staff may seek written informed consent at the receiving hospital; or (b) deferred consent may be sought in the community by post (written informed consent), email or telephone. While seeking deferred consent, staff will be available to answer any questions that the participants may have.

For participants lacking capacity, we will seek consent from their relative or legally authorised representative, which is known as proxy consent.^28^ A research nurse will briefly explain to them that the patient will receive the usual hospital care for TBI. The responsible nurse will also clarify that only basic clinical data will be reported using a CRF to be analysed to improve prehospital care. A brief information sheet will be provided upon request. The ability of participants to provide consent can be assessed at any point during the study period. Participants who regain capacity will be provided with a detailed participant information sheet, and their written consent to continue in this feasibility study will be obtained. If the patient does not regain capacity, we will seek deferred assent from a relative or professional legal representative to retain the patient’s data in the study.

### Data analysis

#### Quantitative data

A descriptive analysis will be conducted based on the baseline data for patients enrolled in the study to characterise the demographic and clinical profile. This will include the number of eligible participants who were approached, the proportion who consented to participate, data completeness (expressed as number and percentage) for each variable collected and number and percentage of participants completing follow-up. We will also report recruitment data as rates (number of participants enrolled per week across the study period).

The interobserver reliability between paramedics and emergency physicians’ use of the CCHR will be calculated using Cohen’s kappa, a statistical method for measuring agreement between two observers, together with 95% CIs. Additionally, we will report upon the CCHR’s diagnostic performance for ruling out clinically significant TBI. This will be achieved by calculating the sensitivity, specificity, positive and negative likelihood ratios with 95% CIs against a reference standard of traumatic intracranial lesion, which will be identified from in-hospital records. Given the nature of this feasibility study, the analyses will be viewed as exploratory, preliminary and will be descriptive in nature. Furthermore, to determine the acceptability of the CCHR, the OADRI average item scores will be calculated, with higher scores indicating greater acceptability.

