**Methods and analysis:**

We will recruit adult patients who are being transported to an emergency department (ED) by ambulance after suffering a mild TBI. Paramedics will prospectively collect data for the CCHR. All patients will be transported to the ED, where deferred consent will be taken and the treating clinician will reassess the CCHR, blinded to paramedic interpretation. The primary clinical outcome will be neurosurgically significant TBI. Feasibility outcomes include recruitment and attrition rates. We will assess acceptability of the CCHR to paramedics using the Ottawa Acceptability of Decision Rules Instrument. Interobserver reliability of the CCHR will be assessed between paramedics and the treating clinician in the ED. Participating paramedics and patients will be invited to participate in semistructured interviews to explore the acceptability of trial processes and facilitators and barriers to the use of the CCHR in practice. Data will be analysed thematically. We anticipate recruiting approximately 100 patients over 6 months.

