The National Institute for Health and Care Excellence (NICE) has guidelines that largely follow the CCHR to determine when to perform CT scans in cases of head injury.^12^ This approach is supported by evidence showing that the CCHR rule is the most cost-effective among various decision rules evaluated.^13^ Although the number of CT scans has increased, the admission rate has been halved (from 9% to 4%), resulting in a saving of £3381 per 100 patients.^14 15^ The implementation of NICE head injury guidelines indicates that the higher costs of CT scans, averaging about £100 per scan, are balanced by the savings from reduced hospital admissions, estimated to be around £847 per patient.^13^

Considering that paramedics have access to all the necessary data for the CCHR, it might be feasible to use the CCHR in the prehospital setting to promote consistency in care and optimise resource utilisation. Prehospital implementation of the CCHR could enable paramedics to transport patients to lower-level or non-trauma centres, or even (if shown to be sufficiently sensitive) safely leave patients at the scene. However, no studies have explored whether clinical decision aids can be used to rule out neurosurgically significant TBI in patients with apparently mild TBI in the prehospital field.

In England and Wales, around 1 million emergency department (ED) visits annually are for head injuries, with 90% being minor (Glasgow Coma Scale (GCS) 13–15), and the majority of patients are transported by ambulance services.^16^ Optimising healthcare resource use and enhancing patient care experiences can be greatly advanced by reducing unnecessary ambulance transports to distant MTCs, when appropriate and feasible.^17 18^ Integrating the CCHR into prehospital field presents a valuable opportunity to improve the triage process, allowing prehospital care providers to make informed decisions regarding the necessity of hospital transport and the level of care required, thereby optimising healthcare resources and potentially reducing healthcare costs. This approach also opens the door to exploring alternative care pathways for such patients, ensuring they receive appropriate and timely care without overwhelming hospital resources.

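### Accuracy is calculated only against traumatic intracranial lesion, so the plan gives no accuracy estimate for its declared clinical outcome, neurosurgically significant TBI

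*Protocol article*

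**What the plan says.** All references are to the protocol article.

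- **Abstract, Methods and analysis:** "The primary clinical outcome will be neurosurgically significant TBI".
- **Introduction:** the evidence gap is whether "clinical decision aids can be used to rule out neurosurgically significant TBI in patients with apparently mild TBI".
- **Outcomes:** the number and proportion of patients with neurosurgically significant TBI is listed as a feasibility outcome.
- **Measuring and defining outcomes:** at least two clinicians review hospital records for "the secondary outcomes of this feasibility study (neurosurgically significant TBI, abnormal CT findings and death within 7 days", blinded to the final reading of the rule. Neurosurgically significant TBI and abnormal CT are separate items in that list. The nearest definition of the former appears under another name: "Neurosurgical interventions are defined as any neurosurgical intervention including intracranial pressure monitoring or an Abbreviated Injury Scale (AIS) with the severity ≥3". That severity grade refers to head injury. Intracranial lesions appear as one component of abnormal CT, alongside skull fractures and other findings.
- **Quantitative data:** "we will report upon the CCHR’s diagnostic performance for ruling out clinically significant TBI". Sensitivity, specificity and both likelihood ratios, with 95% CIs, are then calculated "against a reference standard of traumatic intracranial lesion, which will be identified from in-hospital records". No other reference standard is named.
- **Objectives and Impact:** obtaining an accuracy estimate is the fourth objective, and the accuracy outcomes are expected to inform the design of a fully powered accuracy study.

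**The concern.** A diagnostic accuracy estimate belongs to one target condition. Here the condition that motivates the study, is declared as its clinical outcome and is adjudicated by blinded reviewers does not enter the accuracy calculation. The condition that does enter is introduced only in the analysis section, and the sentence leading up to it uses a third term that is defined nowhere.

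Two things are at stake. A reader could take accuracy for intracranial lesion as evidence about ruling out neurosurgically significant injury, and could carry it into the definitive study as such. And with three terms in use and no stated link between them, the target could be settled after the results are known.

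**Working it through.** **1. Terms side by side**

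| Section | Target named | Use made of it |
|---|---|---|
| Abstract | Neurosurgically significant TBI | Primary clinical outcome |
| Introduction | Neurosurgically significant TBI | Condition to rule out |
| Outcomes | Neurosurgically significant TBI | Number and proportion |
| Measuring and defining outcomes | Neurosurgically significant TBI; abnormal CT; death within 7 days | Adjudicated separately |
| Quantitative data, lead-in | Clinically significant TBI | Claimed target, undefined |
| Quantitative data, calculation | Traumatic intracranial lesion | Only reference standard |

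No section equates any two of these terms, and no 2x2 table against neurosurgically significant TBI is planned.

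**2. Does the article treat the targets as distinct?** Yes. Table 1 ties the high-risk tier of the rule to neurosurgical intervention and the medium-risk tier to brain injury on CT. The definitions also differ: intervention or head AIS of 3 or more on one side, an imaging finding on the other. They overlap, because some lesions will also meet the AIS threshold, but they are not the same set.

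**3. Can the size be taken from the article?** No. It gives no prevalence for either target, no rule-positive rate and no precision target, so there is no stated accuracy figure to reproduce. The only usable input is the planned recruitment of about 100.

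**4. Illustration.** Assume 100 patients and 60 rule-positive. Assume 10 have an intracranial lesion, 9 of them detected, and that 3 of those 10 have neurosurgically significant TBI, all detected. All of these counts except the 100 are assumptions. Intervals are exact (Clopper-Pearson).

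| | Lesion | Neurosurgically significant TBI |
|---|---|---|
| TP / FN / FP / TN | 9 / 1 / 51 / 39 | 3 / 0 / 57 / 40 |
| Sensitivity | 9/10 = 90% (55.5 to 99.7) | 3/3 = 100% (29.2 to 100) |
| Specificity | 39/90 = 43.3% (32.9 to 54.2) | 40/97 = 41.2% (31.3 to 51.7) |
| Negative likelihood ratio | 0.10/0.433 = 0.23 | 0/0.412 = 0 |

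With 50 rule-positive patients, specificity is 54.4% against lesion and 51.5% against neurosurgically significant TBI. With 80 it is 21.1% and 20.6%. In this example the choice of target barely moves specificity. It does move sensitivity, its precision and the negative likelihood ratio, which are what matter for ruling out.

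**5. What a table against the declared outcome could deliver at this size.** If every one of k cases is detected, the lower 95% limit is 0.025^(1/k): 2.5% for k = 1, 29.2% for k = 3, 47.8% for k = 5 and 69.2% for k = 10. The chance of no case among 100 is (1 − p)^100. For assumed prevalences p of 1%, 2%, 3% and 5% this is 36.6%, 13.3%, 4.8% and 0.6%.

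**The case against.** The best defence is that an intracranial-lesion reference is coherent in its own right. The article counts the rule as positive on any high- or medium-risk criterion, the medium tier is aimed at brain injury on CT, and the fourth objective names no target condition. Intracranial lesion is also a component of an adjudicated outcome. This stands as a reason to keep that analysis. It does not supply the missing estimate for the declared outcome.

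Second, the analysis is declared exploratory and descriptive, the limited sample is acknowledged, and nothing in Table 2 (progression criteria) depends on sensitivity, specificity or event counts. That stands and limits the severity. It excuses wide intervals, but not an unsettled target.

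Third, a table against neurosurgically significant TBI may be nearly empty, as step 5 of the working shows. That stands as a cost of the fix.

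A reader might also infer more than the article supports:

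- **That the prevalence of the declared condition is lost, so the definitive study would be sized on a commoner one.** The Outcomes section already has the number and proportion with neurosurgically significant TBI reported. Any contrast in definitive sample size would also need prevalences, a target sensitivity and a margin that the article does not give. The AIS component widens the outcome beyond interventions and could narrow the gap.
- **That calling the outcome primary in the abstract and secondary in the Methods is a contradiction.** It can be read as first among the clinical outcomes and secondary to feasibility. The labels are loose but compatible.

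**Conclusion.** The point holds at moderate severity. The plan reports the frequency of neurosurgically significant TBI but gives no accuracy estimate against it, although that is the declared primary clinical outcome and the condition to be ruled out. The accuracy figures it does produce concern an overlapping but different target, and the sentence introducing them uses an undefined term. The harm falls on the fourth objective and on what is carried into the definitive study. It does not touch the go, amend or stop decision.

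This rests on a comparison of the article's own sections and needs no outside figure. How far the two sets of estimates would differ cannot be fixed from the article. The illustrative counts and the prevalences of 1% to 5% are assumptions, used only to show the direction of the effect and the likely imprecision.

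**What to change.** - **Quantitative data:** add a 2x2 table, with sensitivity, specificity, likelihood ratios and 95% CIs, against adjudicated neurosurgically significant TBI as the reference standard that matches the declared outcome. Keep traumatic intracranial lesion or abnormal CT as a second, separately labelled reference standard, and say which of the two is meant, since the first is only a component of the second.
- **Measuring and defining outcomes:** place the existing definition (neurosurgical intervention including intracranial pressure monitoring, or head AIS of 3 or more) under the name neurosurgically significant TBI. The AIS part is a severity grade and does not belong under a heading of interventions.
- **Throughout:** replace clinically significant TBI with the named targets, and use the same terms and outcome labels in the Abstract, Outcomes, Measuring and defining outcomes, and Quantitative data.
- **Reporting:** state in advance that sensitivity against neurosurgically significant TBI may be very imprecise, and that it will be reported as not estimable if no case occurs.

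Reporting the high-risk tier alone would be an optional extra; it is not needed to resolve the mismatch.

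The cost is a wording change and one more table from outcomes already due to be adjudicated, with no new data collection. The downside is sparse data: at an assumed prevalence of 1% to 3%, the chance of no case in 100 patients is about 37% to 5%.
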